# Safety assessment

## Safety index

### Physical examination

Comprehensive physical examinations are all conducted before treatment, after 8 weeks randomized double-blind treatment period and after the safety observation of 56 weeks.

### Laboratory and auxiliary examination

Before treatment, 8 week randomized double-blind treatment period and observed for 56 weeks after the end of the safety after the end of the period, were

The urine pregnancy test (limited to women of childbearing age), whole blood test, urine routine test test, blood biochemistry (including liver function, renal function, blood glucose, blood lipid and electrolyte) and 12-lead ECG examination were all conducted before treatment, after 8 weeks randomized double-blind treatment period and after the safety observation of 56 weeks.

Because there were renal toxicity of the research drugs in animal experiments, and the adverse reactions of liver were decreased by decreasing the metabolism of losartan reduces *in vivo*. In the present study, examinations of urine routine test test, liver function, renal function and blood electrolyte were conducted with the follow-up 8 weeks once in the fourth week of the randomized double-blind treatment period and the safety observation period to assess the safety of the research drugs.

## Adverse events

### Definition of adverse events

Adverse events (Adverse Event AE) refers to that patients or clinical trial subjects occur adverse medical events after receiving a drug, but it is not necessarily a causal relationship with this treatment.

Significant adverse event (Significant Adverse Event) refers to the addition of serious adverse events, the occurrence of any adverse events caused by application of the corresponding medical measures (such as withdrawal of drugs, reduced dose and symptomatic treatment) and hematologic or other laboratory examination abnormality.

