| **Therapeutic effect index** | **Primary outcome parameters:**   - The changes from baseline in trough mean seated DBP (23 to 26 hours after the morning dose) to the end of the 8-week double-blind treatment period   **Secondary outcome parameters:**   - The change of trough mean seated DBP after 4 weeks treatment - The change of trough mean seated SBP after 4 ,8weeks treatment - Effective rate after 4,8 weeks treatment - The change of trough mean seated SBP/DBP after 4, 8weeks treatment in effective patient - Note: Effective respond was defined as the seated SBP/DBP<140/85mmHg, or seated SBP decrease≥20mmHg and/or seated DBP≥10mmHg. |
| **Safety index** | Adverse events included the abnormal demonstrations of the clinical symptoms after medication and the changes of clinical significances of physical examination, laboratory examination and ECG. |

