| **Statistical analysis** | **Estimation of sample sizes:**  This is a superior efficacy test study. The efficiency test was conducted on the main therapeutic effect index. Setting bilateral α = 0.05, *β* = 0.20, and the standard deviation SD = 7.8 mmHg, the difference of the antihypertensive effect in the two groups were detected as *D* = 3 mmHg. The distribution ratio of the patient cases in the two groups was 1:1. The estimated minimum sample size was 108 pairs. Taking into account of the factors such as dropping, the present research plan included 260 cases into the two groups with 130 cases of patients in the experiment group and the control group, respectively.  **Statistical analysis of the data set:**  Statistical analysis was conducted by using the full analysis set, per-protocol population set and safety data set. The quality control was strictly carried out in the whole process of the data statistics to ensure the authenticity of the assessment of data.  Full analysis set (Full analysis set, FAS): according to the fundamental principle of intention to treat (ITT), all the randomly enrolled subjects with more than one medication administration record and effective evaluation were included in the full analysis set. When selecting full analysis set for analysis, the latest observation LOCF (LOCF) estimation method was adopted for the estimation of the missing values. Full analysis set is the main effectiveness method for the evaluation of population in the present study.  The Per-Protocol set (PPS): PPS included all the subjects with completed prescribed treatment protocal or no serious violations of tests. The exact definition of the serious violations of the scheme will ultimately determined in the data auditing, which generally included the following situations (but they are not limited to these cases): Not meeting the inclusion criteria, having interference treatment after being selected, poor compliance, interview beyond the time window. PP set is a secondary analysis of the crowds of the effectiveness, but if the results were inconsistent with the full analysis set, detailed analysis should be done on the inconsistent results.  Safety data set (Safety Set, SS): the definition of safety data set was the subjects that at least received one time drug treatment.  **Statistical analysis method:**  Statistical analysis was conducted by using the SAS9.13 statistical analysis software for calculation. Quantitative description of the parameters included the calculation of mean, standard deviation, median, minimum value and maximum value. The description of the classified index employed the case number and percentage of the cases.  Descriptive statistics were conducted on the completion of the study. The comparison among groups was conducted on the demographic and baseline characteristics to analyze the equilibrium between groups.  Analysis of the main outcome measures: the main efficacy index will use the test of superiority. In addition, the dereasee value os DBP of each subject after treatment of 8 weeks will also be calculated, and descriptions in each group were done (mean, standard deviation, median, minimum, maximum). Comparisons between groups used analysis of variance considering center effect.  Analysis of the secondary outcome indicators: the center effect was not considered in principle. Comparisons between groups employed the variance analysis, chi-square test or nonparametric statistical method.  Analysis of the safety evaluation: parameters of safety evaluation included adverse events/ adverse drug reaction (ADR)/important adverse events or serious adverse events, physical examination and laboratory examination and a 12-lead electrocardiogram. Detailed description was conducted on the cases of adverse events during the test. The incidence rates of the adverse events between the two groups were summarized and compared. The indexes of laboratory examination were statistically described. The difference between two groups was compared when it was necessary. A detailed description of the laboratory indexes and normal cases before treatments was conducted.  This study did not conduct interim analysis. |

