### Observation, recording and reporting of adverse events/serious adverse events

Researchers should explain to subjects in detail, and ask subjects to reflect the changes of disease after treatment faithfully. Physicians should avoid suggestive question. During the test, it should pay close attention to the adverse events observed, cause analysis, judgment, and follow-up observation and recording.

For any adverse events during the trial, the occurring time, symptoms, severity, duration, treatment measures and prognosis should be recorded in the case report form and to evaluate its correlation with the experimental drugs, and the researchers do a detailed record, signing and dating.

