### The judgment and treatment of parameter abnormalities of laboratory test

Clinical significance of abnormal laboratory data of all researchers must obtain the trial period to evaluate. Must be complete and report any clinically significant laboratory abnormalities, and follow-up to the normal.

Clinical significance is defined as the researchers that have important clinical significance, require medical intervention or meet any abnormal data definition of serious adverse events ". If there are other clinical indications, clinical observation and evaluation, to determine the anomaly results significant or cause or monitoring of adverse events.

Abnormal laboratory can not explain the value, to repeat the examination, and follow-up to the value returned to normal reference range or reach the baseline, and / or find a reasonable explanation. If there is a clear explanation, please record in the case report form.

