## Statistical methods

### Aalysis method

Statistical analysis using SAS9.13 statistical analysis software for calculation. Quantitative description of the calculation of mean and standard deviation, median, minimum value, maximum value. Classification index described by number and percentage of cases.

Completion of the study will be carried out descriptive statistics on the demographics and baseline characteristics were compared between the two groups in a balanced analysis between groups.

Analysis of the main outcome measures: the main efficacy index will adopt non inferiority test. In addition, also calculate each subject after 8 weeks of treatment, DBP decreased and the seat value groups (mean standard deviation, median, minimum and maximum), groups were compared using analysis of variance center effect considered.

Analysis of secondary efficacy indicators: in principle does not consider the center effect, by using variance analysis, chi square test or nonparametric statistical method for comparison between groups.

Analysis of safety evaluation, safety evaluation included adverse events / ADR / important adverse events or serious adverse events, physical examination and laboratory examination and a 12 lead electrocardiogram. Cases of adverse events during the detailed description of test, summary comparison of incidence of adverse events between the two groups. Statistical description and index of laboratory examination and necessary changes were compared between the two groups. A detailed description of laboratory indexes was normal before treatment after treatment of abnormal.

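### Section 9.2.1 misdefines the significant adverse event: cause and effect are reversed, the laboratory part has no clinical-significance limit, and the place of serious events is unclear

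*Protocol*

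**What the plan says.** Section 9.2.1 first defines an adverse event and then, in one sentence, a significant adverse event. That sentence has three parts:

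- Relation to serious events: the term "refers to the addition of serious adverse events".
- Events and measures: "the occurrence of any adverse events caused by application of the corresponding medical measures (such as withdrawal of drugs, reduced dose and symptomatic treatment".
- Laboratory findings: "and hematologic or other laboratory examination abnormality".

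No other section defines the category. It is used in the analysis under another name. Section 11.4.1 states that "safety evaluation included adverse events / ADR / important adverse events or serious adverse events", together with examinations and ECG, make up the safety evaluation, and the statistical part of the protocol summary lists the same items.

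Two other places deal with laboratory findings, and both limit them. The safety index in the protocol summary counts "the changes of clinical significances of physical examination, laboratory examination and ECG". Section 9.2.6 requires investigators to "report any clinically significant laboratory abnormalities" and says what clinically significant means: judged important by the investigator, needing medical intervention, or meeting the definition of a serious event.

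**The concern.** A category between all adverse events and serious adverse events is meant to show tolerability: events that were not serious but had a consequence for treatment. The printed sentence points the other way. It takes events produced by stopping drug, lowering the dose or treating symptoms, and not events that prompted those actions. In a placebo-controlled trial the second group is the informative one.

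The laboratory part has no threshold and no reference to Section 9.2.6, so two investigators could classify the same mildly out-of-range value differently. The opening words leave a third ambiguity: serious events could be read as included in the category or as set apart from it. At stake is the content of one reported safety category and whether sites would fill it in the same way.

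**Working it through.** The point is about wording, so the check sets the passages side by side and then uses the only figures the document gives for the category.

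**1. Literal reading against the protocol's own rules**

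| Case | Section 9.2.1 as printed | Category meant to show non-serious events with consequences |
|---|---|---|
| Non-serious headache, after which the participant stops drug | Not counted: the event preceded the measure | Counted |
| New symptom produced by a symptomatic treatment | Counted: caused by the measure | Not counted on that ground alone |
| Potassium just out of range, judged of no clinical significance | Can be counted: no qualifier | Not counted, following the safety index and Section 9.2.6 |
| Serious adverse event | Undetermined | Must be stated |

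On the last row, Section 11.4.1 lists important and serious events as separate items. That suggests serious events lie outside the category, but it does not settle the point.

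**2. Terms**

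- Sections 9.2.3 and 9.2.4: *serious* in the heading, *significant* in the text.
- Section 9.2.5: *serious* in the body heading, *important* in the table of contents and in the text.
- Protocol summary and Section 11.4.1: *important*.

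A reader has to infer that *significant* and *important* name the same category.

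**3. Reduced dose**

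Section 9.2.1 gives reduced dose as an example of a measure. Section 6.6 states that the dose stays unchanged throughout, with no adjustment. The two must be reconciled.

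**4. What the error does not reach**

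- The comparison that the summary names is this: "The incidence rates of the adverse events between the two groups were summarized and compared". An event that led to stopping drug is an adverse event however Section 9.2.1 is read, so it stays in that rate.
- Section 9.2.2 requires, for any adverse event, that "the occurring time, symptoms, severity, duration, treatment measures and prognosis should be recorded in the case report form". Treatment measures are therefore captured for each event.
- Section 4.3 lists serious or intolerable adverse events among the reasons for exit, so event-led withdrawal is also captured.

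**5. The only figures for the category**

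Section 1.2 reports the earlier Phase II trial. Its arms were 80, 160 and 240 mg and losartan 50 mg.

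- Important adverse events: 8/70 = 11.43%, 10/69 = 14.49%, 8/73 = 10.96%, 11/70 = 15.71%. These match the printed values. Pooled: (8 + 10 + 8 + 11)/(70 + 69 + 73 + 70) = 37/282 = 13.1%.
- All adverse events: (23 + 19 + 22 + 25)/282 = 89/282 = 31.6%.

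The important events there were mainly headache, dizziness, nausea and abnormal liver function. That pattern looks neither limited to events produced by measures nor swamped by laboratory values. The definition used in that trial is not printed, so this does not show how Section 9.2.1 would be applied.

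**The case against.** The strongest reply is that this is a translation slip and nobody would apply it literally. The sentence speaks of corresponding measures, and symptomatic treatment presupposes symptoms, so *leading to* is the natural meaning. The laboratory limit can be borrowed from the safety index and Section 9.2.6. How the category is tabulated may be left to a statistical analysis plan that is not at hand. Much of this stands: the reversal does read as a slip and not as a deliberate choice. But the sentence is the governing text, no other passage corrects it, and rebuilding the category from the data would need a rule that the protocol does not contain.

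Three stronger readings are tempting and are not supported.

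- *A compared rate is distorted.* The comparison named is of adverse-event incidence. The earlier trial's plan was worded in nearly the same way and its important-event rates were then compared, so a reader might expect the same here, but this protocol does not say so.
- *Every laboratory abnormality counts, so a true difference is diluted.* The text does not say every. Any figure for the share of participants with a chance flag would rest on assumed analyte counts, independence and flag rates. Equal flagging in the two arms would be a further assumption, and the earlier trial reported on-treatment changes in creatinine, uric acid and potassium at 240 mg.
- *The category cannot be compared with the earlier trial.* That trial's definition is not printed, so neither sameness nor difference can be claimed.

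**Conclusion.** The definition in Section 9.2.1 is wrong as printed on two counts, causal direction and the missing clinical-significance limit, and unclear on a third, the place of serious events. The consequence is confined to the reported significant (important) adverse event category. Literal use would omit events that led to stopping drug and could admit laboratory values of no clinical significance. No number of misclassified events can be given: the document has no rate for this trial, and the earlier trial's 11% to 16% cannot be carried over without its definition. The overall adverse-event comparison is unaffected, and no event is lost from the data, provided the measures are recorded as Section 9.2.2 requires. The conclusion assumes only that *significant* and *important* name the same category. It is a real definition error, cheap to correct, and no threat to the trial's main safety comparison.

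**What to change.** Reword the sentence in Section 9.2.1 along these lines: *Significant adverse event: any adverse event, other than a serious adverse event, that led to a medical measure, and any haematological or other laboratory abnormality judged clinically significant under Section 9.2.6.* This states the relation to serious events outright.

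Then:

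- choose one term, significant or important, and use it in the headings and text of Sections 9.2.2 to 9.2.5, in Section 11.4.1 and in the protocol summary;
- reconcile the reduced-dose example in Section 9.2.1 with the statement in Section 6.6 that there is no dose adjustment.

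The cost is one sentence, a consistent replacement of terms and a matching note in the case report form instructions. No new data are needed, and the rewording itself changes no treatment rule. If sites had counted laboratory values of no clinical significance, the reported category would lose them.

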### Observation, recording and reporting of adverse events/serious adverse events

Researchers should explain to subjects in detail, and ask subjects to reflect the changes of disease after treatment faithfully. Physicians should avoid suggestive question. During the test, it should pay close attention to the adverse events observed, cause analysis, judgment, and follow-up observation and recording.

For any adverse events during the trial, the occurring time, symptoms, severity, duration, treatment measures and prognosis should be recorded in the case report form and to evaluate its correlation with the experimental drugs, and the researchers do a detailed record, signing and dating.

### Criteria of severity degrees of adverse events/serious adverse events

All adverse events/significant adverse events should be evaluated severity by researchers, and rating should be done according to the criteria of 1 grade (mild), grade 2 (moderate), grade 3 (severe) and 4 grade (life-threatening) standards.

Grade 1 (mild): feeling unwell, but not interfering with daily activities, easily enduring.

Grade 2 (moderate): degree of discomfort is enough to reduce or affect daily activities, may require medical intervention.

Grade 3 (severe): unable to work or engage in daily activities, require medical intervention.

Grade 4 (life-threatening): a great possibility of death when occurrence of the events.

### Criteria of relationship between experimental drugs of adverse events/serious adverse events

Determination of the relationship between adverse events/signiciant adverse events and the test drugs:

Determination according to 5 grade criteria: that is certainly related, may be, may be independent, independent, be unable to be evaluted. The first two are adverse reactions, and the incidence rate of the adverse reaction is analyzed.

Certainly related: the appearance of reaction conforms to the reasonable time order after drug application, and the reaction conforms to the known reaction type of the suspected drugs; improvement after stopping of drug, occurrence of the reaction after repeated administration of the drug.

May be relatd: the appearance of reaction conforms to the reasonable time order after drug application, and the reaction conforms to the known reaction type of the suspected drugs; the patient's clinical status or other treatments may also induce this reaction.

Probably not related: the reaction is not in line with the reasonable time order after drug application, and the reaction is not in line with the known reaction type of the suspected; the patient's clinical status or other treatments may also induce this reaction.

Unrelated: the reaction does not comply with the time sequence after reasonable, a reaction type with non experimental drugs known reaction; the patient's clinical status or other treatments may cause the reaction, improve the state of disease or stop the elimination reaction to other treatments, the repeated use of other treatment response.

Unable to evaluate: the reaction has no relationship with the medication time, type and the drug known reaction similar to that of other drugs may also cause the same reaction.

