**（2）Adverse reactions**

The incidence rates of the adverse reactions in the groups of Allisartan Isoproxil with 80 160, 240mg and losartan of 50mg were 8.57% (6/70), 4.35% (3/69), 9.59% (7/73) and 10% (7/70), mainly manifested as headache, dizziness, headache, nausea, abnormal liver function, of which the incidence rates of headache (4.11%) and headache (2.74%) in the group of the Allisartan Isoproxil (240mg) were the highest. The incidence rates of dizziness, abnormal liver function abd nausea in each dose group were similar. The adverse reactions mainly exhibited as mild, some were moderate, which could be alleviated themselves or alleviated after symptomatic treatments. There was no significant difference in the incidence rate of adverse reactions and severe degrees among groups.

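### The adverse reaction rate leaves out events graded as unable to be evaluated, so it can only understate possible reactions; report it with and without that grade and repair the grade's wording

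*Protocol*

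**What the plan says.** Section 9.2.4 sets the scale: "Determination according to 5 grade criteria: that is certainly related, may be, may be independent, independent, be unable to be evaluted". It then says which grades count: "The first two are adverse reactions, and the incidence rate of the adverse reaction is analyzed". No separate count of the fifth grade is given and no alternative rule is stated. The sentence is not limited to one study period.

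The fifth grade is defined in these terms: "Unable to evaluate: the reaction has no relationship with the medication time, type and the drug known reaction similar to that of other drugs may". The clause ends by naming those drugs as a possible cause. The English is broken, and the clause can be read in more than one way.

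Section 9.2.2 asks that any adverse event "should be recorded in the case report form and to evaluate its correlation with the experimental drugs". The statistical part of the protocol summary lists what is evaluated: "parameters of safety evaluation included adverse events/ adverse drug reaction (ADR)/important adverse events or serious adverse events". It also plans a comparison that does not depend on causality: "The incidence rates of the adverse events between the two groups were summarized and compared". Section 11.4.1 repeats both points.

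**The concern.** A two-way split into reaction and non-reaction has to put the undecided events somewhere. This protocol puts them with the non-reactions, and it does so in a stated counting rule, not by silence. For a safety measure of a new drug that is the less cautious side: an event that the investigator could not attribute either way counts as if it had been judged unrelated.

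The definition makes this harder to accept. The fifth grade appears to cover events that look like a known reaction of the drug but have another drug as a rival explanation. *May be related*, which is counted, also allows a rival explanation. Whether such an event enters the rate may therefore turn on a boundary that the text does not draw clearly. Section 7.2 adds that interactions of allisartan with other drugs have not been studied, so events with a second drug as a possible cause may be hard to judge.

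What is at stake is the adverse reaction rate as a reported figure. The sponsor uses that kind of figure: section 6.6 cites the absence of a difference in adverse reactions in the earlier trial as part of the case for the 240 mg dose.

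**Working it through.** **1. Which grades enter the numerator.** The criteria in section 9.2.4, side by side:

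| Grade | Timing after dosing | Known reaction type of the drug | Another cause possible | Counted |
|---|---|---|---|---|
| Certainly related | Reasonable | Yes | Not mentioned; improves on stopping, recurs on repeat dosing | Yes |
| May be related | Reasonable | Yes | Yes | Yes |
| Probably not related | Not reasonable | No | Yes | No |
| Unrelated | Not reasonable | No | Yes | No |
| Unable to evaluate | Printed as having no relationship | Apparently similar (garbled) | Yes, other drugs | No |

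On the reading in the table, the fifth grade agrees with *may be related* on reaction type and on a rival cause, and differs from it on timing. It differs from *probably not related* on reaction type. It sits between the two, but it is counted with the lower one.

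**2. Direction.** Let r be the patients with at least one event in the first two grades, k the patients whose only possible route into the numerator is a fifth-grade event, and n the patients treated.

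- Rate under the protocol's rule: r/n
- Rate with the fifth grade counted as related: (r + k)/n
- Difference: k/n, which is never negative

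So the protocol's rule lowers the rate or leaves it unchanged.

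**3. Size in the 8-week period.** Section 5.1 plans n = 130 per arm.

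- k = 1: 1/130 = 0.77 percentage points
- k = 3: 3/130 = 2.31 percentage points
- k = 5: 5/130 = 3.85 percentage points

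The protocol gives no k; these values are assumptions, and k = 0 is possible.

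**4. Size in the 56-week period.** The number who continue is not stated. If all 260 did, each such patient would be worth 1/260 = 0.38 percentage points; with fewer, each is worth more.

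**5. The only adverse reaction rates in the protocol.** The background section on the earlier phase II trial gives, for allisartan 80, 160 and 240 mg and losartan 50 mg, "8.57% (6/70), 4.35% (3/69), 9.59% (7/73) and 10% (7/70"). All four reproduce: 6/70 = 8.57%, 3/69 = 4.35%, 7/73 = 9.59%, 7/70 = 10.00%. As an illustration of sensitivity only, the 240 mg figure would become 8/73 = 10.96%, 9/73 = 12.33% or 10/73 = 13.70% with one, two or three further patients counted. The protocol does not say that the earlier trial used this scale or that it had any unassessable events.

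**The case against.** The strongest reply is that nothing is hidden. All adverse events are compared between arms whatever their causality, and important and serious adverse events are listed too. In the 8-week period grading is done under blinding, with identical tablets and the same rule in both arms. The adverse reaction rate carries no hypothesis and no sample size. A prespecified definition of *related* is a legitimate choice, and an extra sensitivity row could sit in a statistical analysis plan that is not shown. Most of this stands, and it limits the reach of the point. It does not remove it: the counting rule is written in the protocol, and an added row elsewhere would leave that rule as the definition of the rate. In the 56-week period there is also no concurrent placebo arm to fall back on, so interpretation leans more on the investigator's causality grade.

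A second reply is that the fifth grade, as printed, denies any relationship with dosing time, while both counted grades require reasonable timing; counting it would override the protocol's own criterion. That is fair as far as the printed words go, and counting every such event can err in the other direction. It supports showing both rates and repairing the wording, not replacing one rule by the other.

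Four stronger readings are tempting, and the documents support none of them:

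- *Missing or blank causality assessments are scored as non-reactions.* The fifth grade is defined by timing, reaction type and a rival cause, not by absent information. Section 9.2.2 requires an assessment for any event, and nothing sends a blank field to this grade.
- *The rate is biased low.* That needs at least one fifth-grade event that was truly drug-related. None is documented.
- *The drug-placebo comparison is weakened.* The rule is the same in both blinded arms, and no differential effect is shown.
- *The effect can be read from the earlier 240 mg arm, between 7/73 = 9.59% with reactions and 22/73 = 30.14% with any event.* That is only the gap between two reported rates. To use it, all 22 − 7 = 15 remaining patients would have to be unassessable and none judged unrelated or probably not related, in a trial not said to have used this scale.

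**Conclusion.** The point holds in a limited form. The protocol's counting sentence handles unassessable events as non-reactions, and the grade they fall into appears to include events resembling the drug's known reactions. The effect on the adverse reaction rate runs in one direction only and amounts to 0.77 percentage points per affected patient in an arm of 130. The total is unknown and may be zero.

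This rests on two assumptions: that the garbled definition means what it appears to mean about reaction type, and that at least one patient has an event of this grade and no counted reaction. The all-cause comparison protects the 8-week assessment. The 56-week period, in which every participant takes 240 mg, is where the rule matters most. The change is worth making because it is cheap and corrects a stated rule.

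**What to change.** Replace the counting sentence in section 9.2.4 with something like: *The adverse reaction rate is reported in two rows: (a) certainly related, may be related and unable to be evaluated, as the conservative rate; (b) certainly related and may be related alone. The number of events and patients graded unable to be evaluated is shown for each arm in the 8-week period, and separately for the 56-week period.*

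Rewrite the definition of the fifth grade so that timing, reaction type and alternative cause are each stated plainly and its boundary with *may be related* is clear.

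The cost is two short text changes and one extra table row with its count, plus an adverse reaction rate that may look slightly less favourable. Treatment and the primary endpoint are not touched.
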